### Laboratory Analysis

All laboratory tests are considered standard and include PSA measurement, peripheral blood cell count with formula, kidney function tests, liver function tests, and testosterone measurement. These laboratory tests are done during every follow-up visit.

### Time Schedule

The aim is to recruit the necessary number of patients within a timeframe of 48 months. Follow-up of these patients will be lifelong to correctly estimate the primary and secondary endpoints. Reports on acute PART-induced toxicity and QoL will be expected within 6 months of the closure of the trial. Furthermore, the primary endpoint will be calculated after a median follow-up of 60 months.

### Safety

This project has been funded by “Kom op tegen Kanker” (study number: S59533). The investigators shall report all serious adverse events (grade 3 or higher) immediately to the sponsor. The immediate report shall be followed by detailed, written reports. The immediate and follow-up reports shall identify subjects by code numbers. For reported deaths of a subject, the investigator shall supply the sponsor and the accredited ethics committee with any additional information requested. Patients will be withdrawn from PART if they develop grade 4 toxicity. Based on former experience in cervical cancer, there is negligible chance for occurrence of grade 4 toxicity when PART is delivered [49].

The investigator shall ensure that all relevant information about suspected unexpected serious adverse reactions that are fatal or life threatening is recorded and reported as soon as possible to the minister, and to the competent ethics committee, and in any case, no later than 7 days after knowledge by the investigator of such a case.

All other suspected unexpected serious adverse reactions shall be reported to the minister and the ethics committee concerned as soon as possible but within a maximum of 15 days of first knowledge by the investigator. Furthermore, the principal investigator shall inform other investigators.

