### Secondary Endpoints

Secondary endpoints are quality of life (QoL), treatment-related acute and late toxicity, time to palliative ADT, time to castration-refractory prostate cancer (CRPC), CSS, and in-field pelvic and para-aortic disease control.

The QoL is measured using the European Organization for Research and Treatment of Cancer (EORTC) core questionnaire [41]. In addition, the EORTC prostate cancer module [42], the EuroQol 5 dimensions questionnaire [43], the International Consultation on Incontinence Short Form score [44], and the International Index of Erectile Function scoring system [45] are used to assess urinary, bowel, and sexual functioning and symptoms and evaluate the side effects of hormonal treatment associated with radiotherapy. QoL questionnaires are handed over to patients before treatment (baseline score) and at well-defined time points (end of treatment; 1 month, 3 months, 6 months, and 9 months after treatment; every 6 months until 5 years after treatment; and every 12 months until 10 years after treatment). QoL results will be presented in accordance with guidelines for reporting health-related QoL outcomes in cancer clinical trials published by the EORTC [46].

Treatment-related toxicity is assessed using the Common Toxicity Criteria for adverse events version 4.0 (CTCAE v4.0) [47]. Abdominal pain, diarrhea, enterocolitis, fecal incontinence, flatulence, hemorrhoids, proctitis, rectal fistula, rectal hemorrhage, rectal pain, noninfectious cystitis, hematuria, urinary frequency, urinary incontinence, urinary retention, urinary tract pain, erectile dysfunction, and fatigue are scored as adverse events according to CTCAE v4.0. Symptoms are scored before treatment. In addition, PART-induced acute toxicity (CTCAE v4.0) is scored weekly during radiation treatment and 1 month and 3 months after treatment. Furthermore, treatment-induced late toxicity (CTCAE v4.0) is scored at 6, 9, and 12 months after treatment; every 6 months until 5 years after treatment; and every 12 months until 10 years after treatment.

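### Immediate reporting to the sponsor ties "serious" to CTCAE grade 3 or higher, while the same section classes serious reactions by outcome; the two usages need reconciling

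*Protocol article*

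**What the plan says.** The rule on reporting to the sponsor is in the Safety section of the protocol article: "The investigators shall report all serious adverse events (grade 3 or higher) immediately to the sponsor". Detailed written reports must follow.

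The only grading scale the article names is in the Secondary Endpoints section: "Treatment-related toxicity is assessed using the Common Toxicity Criteria for adverse events version 4.0 (CTCAE v4.0) [47". The list of scored items there covers bowel, urinary and sexual symptoms and ends with "urinary retention, urinary tract pain, erectile dysfunction, and fatigue are scored as adverse events according to CTCAE v4.0".

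The Safety section uses grade once more, for a different purpose: "Patients will be withdrawn from PART if they develop grade 4 toxicity". It then turns to unexpected reactions. One group is "suspected unexpected serious adverse reactions that are fatal or life threatening", to be reported "no later than 7 days after knowledge by the investigator of such a case". For the rest, "All other suspected unexpected serious adverse reactions shall be reported to the minister and the ethics committee concerned", within 15 days. Neither of these two duties carries a grade cut-off, and neither says separately what serious means.

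**The concern.** Grade and seriousness are different properties of an adverse event. A toxicity grade describes how severe the symptom is. Seriousness describes what the event led to, for example hospital admission or lasting disability. A reporting rule that substitutes one for the other can fail in two directions: it can let through an event of modest grade with a grave consequence, and it can call for immediate reports of events that are severe on the scale but expected and without such a consequence.

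Both matter here. The article presents the trial as the first of elective para-aortic irradiation in prostate cancer, there is no concurrent control group, and the reassurance about grade 4 toxicity is drawn from cervical cancer. How quickly the sponsor learns of a serious event depends on the wording of this one sentence.

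**Working it through.** The plan gives no figure on this point and no arithmetic applies. The check is to set the statements side by side and follow each reading through.

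**How the article uses the terms**

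| Place | Purpose | Criterion |
|---|---|---|
| Safety, first paragraph | Immediate report to the sponsor | Serious, with grade 3 or higher in parentheses |
| Safety, first paragraph | Withdrawal from PART | Grade 4 toxicity |
| Safety, second paragraph | Report within 7 days to the minister and the ethics committee | Unexpected serious reaction that is fatal or life threatening; no grade |
| Safety, third paragraph | Report within 15 days to the same bodies | All other unexpected serious reactions; no grade |
| Secondary Endpoints | Toxicity scoring | CTCAE v4.0 grade |

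No other part of the article describes seriousness. The section therefore ties it to a grade for one duty and uses outcome language for the next, with nothing to connect them.

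**Reading A: the parenthesis defines serious.** An event is serious if and only if it reaches grade 3.

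- An event below grade 3 with a serious outcome does not meet the criterion. No immediate report is required.
- A grade 3 event that is expected and has no serious outcome does meet it. An immediate report and a written follow-up are required. Erectile dysfunction and fatigue are both on the scored list, all patients are planned to receive 24 months of androgen deprivation, and men who have had prostatectomy are eligible.

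**Reading B: the parenthesis restricts serious.** Only events that are serious by some unstated criterion and also reach grade 3 are covered.

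- An event below grade 3 with a serious outcome still fails the grade condition. No immediate report is required.
- A grade 3 event without a serious outcome is not covered, so there is no over-reporting.

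**Result.** The gap for lower-grade events follows under both readings. The surplus of immediate reports follows only under reading A.

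**What else could capture a lower-grade serious event**

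1. Scheduled toxicity scoring. Items on the list are scored before treatment, weekly during radiotherapy, at 1 and 3 months, and then on a fixed schedule up to 10 years. An event on the list is still recorded; what is lost is immediate notice to the sponsor.
2. The 7-day and 15-day routes. These run from the investigator's own knowledge and have no grade threshold. They can capture a lower-grade event, but only one that is suspected, unexpected and judged serious. For the 15-day route that judgement has no stated criterion.

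**The case against.** The strongest reply is that this is a journal article condensing a fuller protocol, which the article itself refers to, and that a full definition of a serious adverse event commonly sits there. That is fair as far as it goes: if the article were silent on the definition, there would be no finding. It is not silent. It gives a criterion, and the criterion is a grade. If the full protocol does define seriousness by outcome, the published sentence conflicts with it and still needs correcting.

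A second reply is that the parenthesis may be a restriction and not a definition. This stands, and it makes the over-reporting half conditional. It does not touch the under-reporting half.

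A third reply is that whether an event below grade 3 can lead to hospital admission or lasting disability depends on the CTCAE v4.0 grade criteria, which the article cites but does not reproduce. This also stands. It means that the number of events missed cannot be judged from the document; it does not make the wording sound.

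Three stronger inferences are tempting, and the document does not support them.

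- A reader might infer that the 7-day and 15-day duties carry the same fault. They have no grade cut-off, and the 7-day duty names its outcomes. The most that can be said is that the 15-day duty relies on a word which the article describes only by grade.
- A reader might infer that immediate reporting is the trial's main safety signal, so that missed events are lost altogether. Acute and late toxicity is a secondary endpoint, scored on schedule to 10 years, with incidence and Kaplan-Meier risk estimates planned.
- A reader might try to turn the enrolment target of 151 into a count of surplus reports. That figure counts men, not reports, and the article gives no rate of grade 3 scores without a serious outcome.

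**Conclusion.** The point holds in a limited form. The Safety section ties seriousness to a severity grade for immediate reporting to the sponsor and to outcome for the fastest report to the authorities. The consequence that holds on either reading is that an event below grade 3 with a serious outcome need not be reported immediately to the sponsor. The further consequence, immediate reports of expected grade 3 scores that are not serious by outcome, holds only if the parenthesis is the definition, which is its plainer reading.

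The size of either effect cannot be estimated: the document gives no event rates and no grade criteria. The conclusion assumes only that severity and outcome do not always coincide. Many events of grade 3 or higher will also be serious, so the two sets overlap. The sample size and the primary analysis are unaffected. The defect concerns the speed and selectivity of safety reporting, and it is worth correcting because correction is cheap.

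**What to change.** In the Safety section, replace the parenthesis with a definition of a serious adverse event by outcome, applying regardless of grade. State that the same definition governs the immediate report to the sponsor and the 7-day and 15-day reports. Make toxicity of grade 3 or higher a separate category with its own listing, so that severity information is kept without standing in for seriousness. If the full protocol already holds an outcome-based definition, bring the published sentence into line with it.

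The cost is a short rewording of the Safety section and a matching change to the reporting form. No patients, visits or analyses are added.

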### Sample Size and Statistics

We aim to improve 5-year cRFS by 15% (primary endpoint). This would result in a 5-year cRFS of 75% compared with the control group with WPRT only that reaches a 5-year cRFS of 60% [18,20]. For a log-rank test comparing two survival curves with a one-sided significance level of .1, assuming uniform accrual with an accrual time of 48 months and a follow-up time of 12 months, a sample size of 137 is required to obtain a power of at least 80%. Taking into account a dropout of 10%, we aim to include 151 patients. The control group consists of pN1 patients treated with adjuvant ADT and WPRT alone from whom the data have been published before [20]. The incidence of acute and late toxicity will be recorded. In addition, actuarial risk estimates for developing acute and late toxicity will be calculated using Kaplan-Meier analysis. Time to palliative ADT, time to CRPC, CSS, and in-field pelvic and para-aortic disease control will be calculated using Kaplan-Meier actuarial analysis. cRFS, time to CRPC, CSS, and in-field pelvic and para-aortic disease control times are defined from the date of LN dissection until an event or last follow-up. Statistical analysis will be performed using the latest version of SPSS (IBM Corp, Armonk, NY, USA).

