## Abstract

**Background:**

In patients with prostate cancer (PCa) with histopathologically proven pelvic lymph node (LN) metastasis (pN1) after extended pelvic lymph node dissection (ePLND), multimodality treatment consisting of treatment of the primary tumor and whole pelvic radiotherapy (WPRT) combined with androgen deprivation therapy (ADT) offers promising results, leading to better cause-specific survival rates compared with ADT alone. However, in case more than one pelvic LN is invaded by the tumor, approximately 40% of the patients relapse biochemically and clinically. Clinical relapse is present in the para-aortic LNs (M1a disease) in up to 77% of the relapsing cases.

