## Introduction

Prostate cancer (PCa) is the most common nonskin malignancy and an important cause of cancer-related mortality in men in industrialized countries worldwide [1,2]. Mortality is highest in patients with high-risk PCa, defined by the guidelines of the European Association of Urology (EAU) as T-stage ≥cT2c or Gleason score ≥8 or prostate-specific antigen (PSA) >20 ng/mL. These patients benefit from aggressive local treatment (surgery with or without adjuvant radiotherapy or primary radiotherapy). To assess the risk of disease spread to pelvic nodes, predictive nomograms are used [3-5], although the EAU guidelines consider an extended pelvic lymph node dissection (ePLND) as a necessity in high-risk patients [6]. Indeed, ePLND has proven to be the most accurate nodal staging procedure and, therefore, remains the gold standard [7] with even a positive effect on PCa mortality, certainly in case of limited nodal disease [8] and negative nodes [9].

Historically, patients with positive pelvic lymph nodes (LNs; N1) were considered metastatic and treated with lifelong palliative androgen deprivation therapy (ADT) only [10]. However, in the 21st century, an important paradigm shift occurred. First, local treatment with curative intent is gaining interest in patients with N1 disease [11]. Hereby, also the extent of ePLND plays a crucial role in predicting cause-specific survival (CSS) as demonstrated by Abdollah et al [12]. Second, large retrospective series demonstrated an improvement in prostate cancer-specific survival (PCSS) when postoperative radiotherapy was added to ADT in pathologically node-positive (pN1) patients [13-15].

In the multidisciplinary approach for pN1 patients, multimodality treatment consisting of treatment of the primary tumor, long-term ADT, and whole pelvic radiotherapy (WPRT) has become the standard of care at the Leuven University Hospitals (LUH; Leuven, Belgium) and at the Ghent University Hospital (GUH; Ghent, Belgium). WPRT is delivered using intensity-modulated or volumetric modulated arc therapy (IMAT/VMAT) [16,17]. Clinical results demonstrated that this multimodality treatment is well tolerated and results in 5-year PCSS of >90%, with the best results observed in patients having a low number of positive LNs. Indeed, patients presenting with 1 or 2 positive LNs had a 5-year PCSS comparable to that of pN0 patients [18-20].

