The number of pathologically metastatic LNs is a determinant for patient outcome. In case >2 LNs are pathologically invaded by the tumor, 30%-40% of the patients relapse biochemically and clinically [21,22]. Furthermore, some data suggest that extracapsular extension of pelvic nodal metastases is an important negative prognostic factor in pN1 patients [23].

Reportedly, clinical relapse (cR) is present in the para-aortic LNs (PALN, M1a disease) in up to 77% of the cases [24,25]. Rischke et al demonstrated the retroperitoneum to be the most frequent site of relapse after pelvic salvage treatment [26]. In the TNM classification, patients with positive PALN are denominated M1a disease and considered as a separate entity [27]. We hypothesize that these positive PALNs will lead to further hematogenous spread (M1b-M1c disease [27]) and that elective para-aortic irradiation will decrease the rate of further metastatic spread, postpone the need for palliative ADT, and prolong the time to castration-refractory disease. To test this hypothesis, we designed a prospective, nonrandomized phase II trial to evaluate the efficacy of elective para-aortic radiotherapy (PART) in pN1 patients compared with those who were historically treated with adjuvant WPRT alone (Figure 1).

This trial is novel and unique as it is the first to investigate the irradiation of the PALN region in pN1 patients with PCa to prevent further metastasis. This strategy has already been evaluated in advanced cervical cancer, but to the best of our knowledge, never in patients with PCa.

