## Results

Ethical approval to conduct this study (version 2.0 from December 1, 2016) was granted by the Medical Ethics Committee University Hospitals/Catholic University Leuven (14/12/2016). Written informed consent of patients is mandatory before recruitment. Recruitment of patients started in 2017 and is expected to be completed by March 2020.

As a result of the PART trial, we will publish the 5-year cRFS, defined as the absence of any cR that would be visible at top of the line imaging, our primary endpoint. Furthermore, we will compare these results with the 5-year cRFS of a historical control group of patients who underwent WPRT; the results of this historical control group have already been published by Poelaert et al [20]. This control group includes patients with PCa who underwent PLND and pelvic radiotherapy between January 2000 and January 2016 at a tertiary center (GUH). Those patients were rigorously treated by several authors of this manuscript ([name], VF, [name], and NL). A total of 154 pN1 patients with PCa who received WPRT were included. As described in the “Sample size and Statistics” section, survival curves of both groups will be compared using log-rank test. Besides, acute toxicity and QoL results will be published after short-term follow-up, whereas treatment-related late toxicity and QoL results, time to palliative ADT, time to CRPC, CSS, and in-field pelvic and para-aortic disease control will be published after a longer follow-up period.

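### The 60% control rate and the log-rank comparator come from a series of pN1 men with no nodal criterion stated, while PART enrols only men meeting one, so the comparison is confounded by nodal case mix in an unknown direction

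*Protocol article*

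**What the plan says.** Protocol article, Methods, Sample Size and Statistics: the goal is a 15-point gain, to a 5-year cRFS of 75%, "compared with the control group with WPRT only that reaches a 5-year cRFS of 60" per cent, citing references 18 and 20. The design statement is "For a log-rank test comparing two survival curves with a one-sided significance level of .1", with 48 months of uniform accrual and 12 months of follow-up, and "a sample size of 137 is required to obtain a power of at least 80" per cent. The same paragraph names reference 20 alone as the source of the control group.

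Results: that group had lymph node dissection and pelvic radiotherapy at one tertiary centre between 2000 and 2016. "A total of 154 pN1 patients with PCa who received WPRT were included". No nodal criterion beyond pN1 is given, and the survival curves of the two groups are to be compared by log-rank test.

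Methods, Inclusion and Exclusion Criteria: pN1 is not enough for entry to PART. One of three conditions must also hold: two or more positive nodes, a positive-to-removed ratio above 7%, or extracapsular extension in any node.

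Introduction: the number of metastatic nodes is described as determining outcome, extracapsular extension is named as an adverse factor, and in the WPRT series (references 18-20) "patients presenting with 1 or 2 positive LNs had a 5-year PCSS comparable to that of pN0 patients".

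**The concern.** In a nonrandomised comparison the control rate does two jobs. It is the planning input, and it is the yardstick against which the result is read. Both need it to estimate what PART-eligible men would have achieved with WPRT alone. The plan takes it from a group defined more broadly than the trial population, and the defining difference is nodal burden, which the protocol itself regards as prognostic.

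The log-rank test described in Sample Size and Statistics and in Results does not remove that difference. A gain over 60%, or the lack of one, could then partly reflect who was enrolled rather than para-aortic irradiation. The trial is meant to support a decision on a randomised phase III study, so the size and sign of that component matter.

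**Working it through.** **1. The plan's own figure.** Inputs from Sample Size and Statistics: 60% versus 75% at 5 years, one-sided 0.10, 80% power, 48 + 12 months. With exponential survival, HR = ln 0.75 / ln 0.60 = 0.563. The event probability with accrual A = 4 and minimum follow-up F = 1 year is p = 1 − [exp(−λF) − exp(−λ(A+F))]/(λA), with λ = −ln S(5)/5. This gives 0.259 for control and 0.157 for PART.
- Lakatos-type log-rank: 136.4 per arm, rounded up to 137, with power 80.1%.
- Freedman: 57.7 events / (0.259 + 0.157) = 139 per arm.
- Schoenfeld: 54.7 events / (0.259 + 0.157) = 132 per arm.

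So 137 reproduces as a per-arm size, and the arithmetic is sound given 60% and 75%.

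**2. Who differs between the groups.** A man with two or more positive nodes always qualifies for PART. A one-node man qualifies by ratio only if few nodes were removed: at the minimum representative harvest of 14, 1/14 = 7.14% qualifies, while 1/15 = 6.67% does not. The pN1 men whom PART excludes on nodal grounds are therefore those with one positive node, a ratio of 7% or less, and no extracapsular extension. Nothing in Results says such men were removed from the 154.

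**3. Direction.** Let f be the eligible share of the controls, e their 5-year cRFS and u that of the ineligible. If 60% is the rate of all controls, 0.60 = f·e + (1−f)·u, so 0.60 − e = [(1−f)/f]·(u − 0.60). If ineligible men do better (u > 0.60), eligible controls lie below 60%. Neither f nor u is in the documents. Assuming u = 80%, an ineligible share of 10% gives 0.111 × 20 = 2.2 points, and 30% gives 0.429 × 20 = 8.6 points. If the 60% instead reflects a group with heavier nodal disease than PART's, the sign reverses. Citing two series for the 60% but using one as comparator leaves this open.

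**4. What a shift would do.** Assume a 5-point shift, follow-up spread evenly over 36-84 months in both groups (midpoint 60, matching the analysis time in Time Schedule), 137 PART men and 154 controls at 60%. Schoenfeld: power = Φ(√(d·a(1−a))·|ln HR| − 1.282), where d is the number of events and a the control fraction. Event probabilities from the formula in step 1 with F = 3: 0.396 at 60%, 0.445 at 55%, 0.347 at 65%, 0.298 at 70%.
- *Eligible WPRT-only rate 55%, PART truly 70%.* Against 60%: HR = ln 0.70/ln 0.60 = 0.698, d = 154 × 0.396 + 137 × 0.298 ≈ 102, power ≈ 70%. Against 100 eligible controls at 55%: HR = 0.597, d ≈ 85, power ≈ 86%.
- *Eligible WPRT-only rate 65%, PART has no effect.* Against 60%: HR = ln 0.65/ln 0.60 = 0.843, d = 154 × 0.396 + 137 × 0.347 ≈ 108, probability of a significant result ≈ 35% instead of 10%.

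**The case against.** The best defence is that the 60% is presented as the rate the WPRT control group reaches, with the control series among its sources. If the 154 men do have 60%, the figure describes the comparator, and 137 follows from it. That stands. An article also condenses, and control selection may be set out in the full protocol or analysis plan. That is fair, but the article fixes both the baseline and the comparator, and describes neither in terms of PART's nodal criteria.

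Two stronger readings are tempting and are not supported.

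*That 60% was borrowed from heavily node-positive men.* The Introduction says "In case >2 LNs are pathologically invaded by the tumor, 30%-40% of the patients relapse biochemically and clinically", and 60% is the complement of the upper end. But that statement rests on references 21 and 22, gives no time horizon, and covers biochemical as well as clinical relapse. The Abstract attaches the figure to a different threshold: "in case more than one pelvic LN is invaded by the tumor, approximately 40% of the patients relapse biochemically and clinically". The numerical match may be coincidence. The favourable statement about men with one or two nodes concerns cancer-specific survival, not relapse.

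*That the 80% power is wrong because the true control rate is higher.* Rates of 65-75% are assumptions. At 137 per arm and 48 + 12 months, what happens depends on what is held fixed:
- Keeping the 15-point gain, power is 82% (control 65%) or 85% (control 70%).
- Keeping HR 0.563, it is 75%, 70% or 64% (control 65%, 70%, 75%).
- Holding PART at 75%, it is 56% or 29% (control 65%, 70%), but that simply assumes a smaller effect than planned.

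At a median follow-up of 60 months, with 137 versus 154 and the hazard ratio kept, Schoenfeld gives 91%, 87% and 82% for controls at 65%, 70% and 75%.

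**Conclusion.** The point holds as one of confounding and of an unanchored benchmark. The documents do not show that 60% is the WPRT-only 5-year cRFS of PART-eligible men, and the planned comparison uses controls for whom no matching nodal criterion is stated. The direction is not established. On the plainest reading, with 60% as the rate of all pN1 controls, eligible controls may do worse and PART's benefit would be understated.

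The size cannot be computed from the documents. The 2 to 9 points, the 70% power and the 35% error above illustrate assumed case-mix differences and do not estimate them. They rest on exponential survival and on an assumed follow-up pattern for the controls. The stated sample size and power are arithmetically correct for their inputs. The change is worth making because the bias, whichever way it runs, is not reduced by more patients or longer follow-up.

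**What to change.** In Sample Size and Statistics and in Results:
- Restrict the comparator to control patients who meet the three-way nodal criterion in Inclusion and Exclusion Criteria.
- Report their Kaplan-Meier 5-year cRFS with 95% CI as the baseline in place of 60%.
- Restate the target cRFS, hazard ratio and power from that value and the actual number of eligible controls.

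As a minor wording point, reconcile the Abstract (more than one node, about 40%) with the Introduction (more than two nodes, 30%-40%).

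Cost: a reanalysis of an already published series treated by several of the authors, with no extra patients. There will be fewer controls, and the stated power may look less favourable. For illustration, at 60% versus 75% with 36-84 months of follow-up and 137 PART men, the event probabilities are 0.396 and 0.248. With 154 controls d ≈ 95 and power is about 93%. With 100 controls d ≈ 74 and power is about 87%.
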